## Assignment of interventions: allocation

### Sequence generation {16a}

The order of interventions will be defined by random envelope picking of participants after successful passing of screening tests. Given three study arms (C, SD, SR), there are six different possible orders of interventions. Each order will be performed four times in an equal ratio. The first 18 participants will pick their respective assignment envelope from box A which contains all possible orders in triplicates (3:3:3:3:3:3), thus guaranteeing an equal allocation ratio until the minimum sample size is reached. The remaining participants will draw from box B, where each order is contained once (1:1:1:1:1:1).

### Concealment mechanism {16b}

Concealment is ensured by paper assignments kept in sealed, opaque envelopes.

### Implementation {16c}

The sponsor of the study will prepare the assignment envelopes. As he is not part of enrolling and assigning procedures, this allows for allocation concealment.

## Assignment of interventions: blinding

### Who will be blinded {17a}

Due to the nature of the study interventions, neither participants nor study personnel can be blinded. To ensure an unbiased rating of participants, outcome assessors of respective performance tests will be blinded.

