### Trial design {8}

This is an exploratory, monocentric, controlled, randomized, crossover, clinical study to detect potential biomarkers. Each participant will be allocated in randomized order to each of the three study arms (control, sleep restriction, and sleep deprivation). Due to the nature of the study, blinding is not possible among participants and study personnel. Test assessors will be blinded, however.

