### Procedure for unblinding if needed {17b}

N/a. Since participants and study personnel cannot be blinded, there is no unblinding. Outcome assessors must be kept blinded even after tests to prevent biased ratings of following participants.

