## Data collection and management

### Plans for assessment and collection of outcomes {18a}

All data and biological specimens will be collected by trained study personnel. Standard operating procedures (SOP) for each study activity ensure consistent and high data quality. Participants will familiarize themselves with the equipment and performance tests (especially the driving simulator) during screening to prevent learning effects during the study sessions.

For the primary outcome, unstimulated oral fluid will be collected using neutral Salivette® (Sarstedt, Sevelen, Germany) sampling devices. Samples will be stored at − 80 °C until trial conclusion and then extracted and analyzed in an untargeted metabolomics approach by ultra-performance liquid chromatography coupled to high-resolution mass spectrometry (UPLC-HRMS) equipment.

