For the secondary outcome measures, different procedures for data collection and assessment will be applied:i.Driving simulation will take place in a custom-modified full-chassis BMW i3 car, in which actuators replace shock absorbers to convey motion cues, such as road bumps, acceleration and braking. Placed in a 270-degree-projection and 360-degree-visibility setting, participants will drive through a fully immersive simulated environment provided by the driving simulation software (SILAB, “Szenariopaket Driver Fitness and Ability” Version 7.0; Würzburg Institute for Traffic Sciences GmbH, Veitshöchheim, Germany), offering a row of validated scenario modules. SILAB simultaneously records vehicle and driving parameters to evaluate, among others, standard deviation of the lateral position (SDLP). Standard driving errors are recorded automatically via Standardized Application for Fitness to Drive Evaluations (S.A.F.E.) software. Additionally, S.A.F.E. allows including observed qualified errors and scoring the driving performance (Fitness to Drive, FtD) [17–19]. Participants perform a two-part customized driving task. An approximately 12-min-long, highly monotonous car following task in a nighttime scenario, including a sound-based vigilance task [18], followed by an approximately 8-min-long, early-morning rural road scenario.ii.The PVT will be performed on laptops and its results will be calculated according to the validated protocol [20].iii.The d2 Test of Attention will be performed on paper and its results will be calculated according to a standardized manual [21, 22].iv.Visual attention test will be performed using virtual reality glasses according to standardized procedure and assessment [23].v.Paper-based Karolinska Sleepiness Scale (Version A) questionnaires will be provided and assessed according to the validated procedure [24].vi.Validated Stanford Sleepiness Scale questionnaires will be completed on laptops and follow a simple seven-scale choice [25].vii.The EEG data, complemented by the polysomnographic (PSG) recording of electrooculogram (EOG), electromyogram (EMG), and electrocardiogram (ECG), will be collected with SIENNA® Ultimate amplifier systems (EMS Biomedical, Korneuburg, Austria) and analyzed with dedicated software for the visual scoring of sleep variables (e.g., alphatrace NeuroSpeed-PSG, alpha trace medical systems, Vienna, Austria). During the driving simulation, EEG data will be recorded using a mobile Philips ALICE 6 device (Philips AG Sleep and Respiratory Care, Zofingen, Switzerland). According to standard international criteria, sleep stages will be scored for each night in the laboratory, and validated sleep variables reflecting sleep quality (e.g., total sleep time, sleep latency, length of non-rapid-eye-movement (NREM) and rapid-eye-movement (REM) sleep stages, waking time after sleep onset, sleep efficiency) will be derived and compared between the conditions [26]. Labmade software will be used for the quantitative analysis of the EEG.viii.Blinded and pre-instructed assessors will collect the behavioral abnormalities of participants after the driving simulation test on paper. They will rate orientation, coordination, speech, mood, appearance, reaction, and eye reactions to light according to standardized options.ix.Unstimulated finger sweat will be collected using self-punched sampling units made of filter paper. Samples will be handled and analyzed analogously to oral fluid samples.x.Exhaled breath samples will be collected in specialized devices from SensAbues AB (Stockholm, Sweden) and BreathExplor® (Munkplast AB, Uppsala, Sweden). Dried blood spots will be collected on volumetric cards (Capitainer, Solna, Sweden). All samples will be handled and analyzed analogously to oral fluid samples.

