### Methods in analysis to handle protocol non-adherence and any statistical methods to handle missing data {20c}

Missing datasets due to participants’ withdrawal from the trial will not be imputed. However, if two of the three study datasets are complete (especially if the control condition is available), these can still be used for two-sided study arm comparisons.

Missing data in metabolic feature tables are common. Typical imputation strategies (e.g., gap filling) in the field of metabolomics are already incorporated in raw data processing software. Therefore, processing parameters will be reported in detail.

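### Section {17a} blinds only performance-test assessors and states no blinding for visual EEG scoring or metabolomics data processing, although its reason covers only staff in contact with participants

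*Protocol article*

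**What the plan says.** Section {17a} of the protocol article gives the general rule, "Due to the nature of the study interventions, neither participants nor study personnel can be blinded", and one exception: "To ensure an unbiased rating of participants, outcome assessors of respective performance tests will be blinded". The trial design section {8} puts the exception more briefly: "Test assessors will be blinded, however". Section {17b} treats unblinding as not applicable and adds: "Outcome assessors must be kept blinded even after tests to prevent biased ratings of following participants".

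In section {18a}, the only procedure that names blinded assessors is the behavioral rating after the drive: "Blinded and pre-instructed assessors will collect the behavioral abnormalities of participants after the driving simulation test on paper". The polysomnographic recordings are "analyzed with dedicated software for the visual scoring of sleep variables", and the resulting sleep variables are compared between conditions. For the primary outcome, "Samples will be stored at − 80 °C until trial conclusion and then extracted and analyzed in an untargeted metabolomics approach". On the handling of the metabolomics data, section {20c} refers to gap filling within the processing software and says that "processing parameters will be reported in detail".

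**The concern.** A sleepless night cannot be hidden from the man who stays awake or from the staff who supervise him. That argument ends when the session ends. Someone who stages a stored recording, or sets processing parameters for samples thawed after the trial, need not know which condition the material came from. Yet the rule covers study personnel as a whole, and the exception reaches only performance tests.

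The two steps left outside the exception involve later judgement. Visual sleep staging has borderline decisions. Untargeted metabolomics requires choices on processing parameters, gap filling and which features to keep. If the arm is known when these choices are made, they can be pulled, without intent, towards the expected difference. For the primary outcome, such choices come before the statistical testing, so the false discovery rate correction does not protect against them.

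**Working it through.** The point has no numerical core, and the plan gives no figure to reproduce. The check is to set the sections side by side.

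1. **Reach of the reason.** Section {17a} rests on the kind of intervention, which concerns people present while it is delivered. The plan itself shows that personnel can be separated: section {18a} has blinded assessors meet the participants face to face after the drive. Masking people who see only a file or a vial is easier than that.

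2. **Reach of the exception.** Sections {8} and {17a} name test assessors and performance tests. Section {17b} justifies keeping the blind by the ratings of later participants. Neither the EEG outcome nor the oral fluid metabolome is a performance test or a rating of a participant.

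3. **Whether another section closes the gap.**
   - Section {27} has files, labels and specimens carry only the participant's ID number. The trial is a crossover and each man receives one ID after consent, so the ID hides the person and not the condition.
   - Section {21a} places the analysis under a statistician independent of sponsor and funder. Independence is stated; blinding is not.
   - Section {17b} describes no unblinding, so the text contains no arm key and no point of release.

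4. **Where judgement enters.**
   - EEG: sleep is staged visually, and outcome vii in section {12} also covers wake EEG, including the drive.
   - Metabolome: the UPLC-HRMS measurement is instrumental. The exposed part is processing and curation. Section {20c} promises that the parameters will be reported; it does not say that they will be fixed beforehand.
   - Section {20a} states the Benjamini–Hochberg correction for the mixed-model route. The pattern-check route also adds features to the shortlist, and no correction is stated for it there.

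5. **Where masking can work.** From section {11a}, the sleep opportunity in the laboratory is:

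| Night | Control | Restriction | Deprivation |
|---|---|---|---|
| Experimental | 8 h | 6 h | 0 h |
| Following night | 8 h | 8 h | 8 h |

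In the experimental night the recording itself gives the arm away: there is none of sleep after deprivation, and a shorter one under restriction. In the following night the scheduled length is equal, so a code can hide the arm at least in principle. Wake and driving EEG, and all specimens, can also be coded. The group comparisons and the classification task in section {20a} need arm labels, so masking must end before them.

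**The case against.** The strongest reply is that silence is not unblinding. Nothing in the article says that EEG scorers or laboratory staff will see the arm. The term study personnel may be meant for those running the sessions. Section {18a} refers to standard operating procedures for each activity, and sample coding or scorer masking is the kind of detail a condensed article leaves to them. This stands in part. A reader might infer that scoring and processing will be done unblinded, and the documents do not support that. They support only that no blinding is provided for these steps. The point survives because {17a} is the section that defines who is blinded: it gives a general rule, a reason and a bounded exception, and the reason does not carry the rule as far as it is stated.

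A second reply is that masking is neither free nor complete. This stands. It needs a code list, a key holder and an unlocking step. It cannot work for experimental-night sleep EEG, and rebound sleep may make a recovery night after deprivation recognisable.

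A third reply is that the risk to the primary outcome is small. Measurement is instrumental, gap filling sits in the software, and no manual curation by arm is described. The first two parts lower the risk without removing it, because parameters and feature filters are still chosen by people. The last part is correct, and no such curation is alleged here.

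Finally, the trial is exploratory, its candidates are to be verified later, and EEG is one of eleven secondary outcomes. That limits the consequence and argues for a low priority.

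**Conclusion.** The point holds as a gap in the stated blinding. Section {17a} uses a reason that fits staff in contact with participants to cover all study personnel, and provides blinding only for performance-test assessors. Visual EEG scoring and the processing of the primary metabolomics data fall outside it, and no other section brings them in.

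The size of any bias cannot be computed. The documents give no scoring agreement, no processing settings and no account of who will know the arm. The conclusion assumes that {17a}, with {8} and {17b}, is the complete statement on blinding, and that operating procedures not shown do not already mask the arm. If they do, one sentence in {17a} settles the matter. This is a desirable improvement and does not threaten the trial's validity.

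**What to change.** Change section {17a} in three ways.

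- Limit the statement that blinding is impossible to participants and to staff in contact with them during sessions.
- Give specimens random codes that hide arm and session. Do the same for EEG recordings that do not themselves reveal the arm: recovery-night, wake and driving EEG. Scorers and data-processing staff work only on these codes. State openly that experimental-night sleep EEG cannot be masked.
- Have the key held outside scoring and processing, for example by the independent statistician named in {21a}. Release it only after the EEG scores and the processed feature table (parameters, gap filling, curation) are locked, and before the group comparisons and the classification task, which need arm labels. Amend {17b} to describe this release.

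The cost is a code list, a key holder and a short delay at unlocking. It needs no additional measurements or participants. Recovery nights after deprivation may still be recognisable to an experienced scorer, so the protection for that part of the EEG is partial.

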### Procedure for unblinding if needed {17b}

N/a. Since participants and study personnel cannot be blinded, there is no unblinding. Outcome assessors must be kept blinded even after tests to prevent biased ratings of following participants.

## Data collection and management

### Plans for assessment and collection of outcomes {18a}

All data and biological specimens will be collected by trained study personnel. Standard operating procedures (SOP) for each study activity ensure consistent and high data quality. Participants will familiarize themselves with the equipment and performance tests (especially the driving simulator) during screening to prevent learning effects during the study sessions.

For the primary outcome, unstimulated oral fluid will be collected using neutral Salivette® (Sarstedt, Sevelen, Germany) sampling devices. Samples will be stored at − 80 °C until trial conclusion and then extracted and analyzed in an untargeted metabolomics approach by ultra-performance liquid chromatography coupled to high-resolution mass spectrometry (UPLC-HRMS) equipment.

For the secondary outcome measures, different procedures for data collection and assessment will be applied:i.Driving simulation will take place in a custom-modified full-chassis BMW i3 car, in which actuators replace shock absorbers to convey motion cues, such as road bumps, acceleration and braking. Placed in a 270-degree-projection and 360-degree-visibility setting, participants will drive through a fully immersive simulated environment provided by the driving simulation software (SILAB, “Szenariopaket Driver Fitness and Ability” Version 7.0; Würzburg Institute for Traffic Sciences GmbH, Veitshöchheim, Germany), offering a row of validated scenario modules. SILAB simultaneously records vehicle and driving parameters to evaluate, among others, standard deviation of the lateral position (SDLP). Standard driving errors are recorded automatically via Standardized Application for Fitness to Drive Evaluations (S.A.F.E.) software. Additionally, S.A.F.E. allows including observed qualified errors and scoring the driving performance (Fitness to Drive, FtD) [17–19]. Participants perform a two-part customized driving task. An approximately 12-min-long, highly monotonous car following task in a nighttime scenario, including a sound-based vigilance task [18], followed by an approximately 8-min-long, early-morning rural road scenario.ii.The PVT will be performed on laptops and its results will be calculated according to the validated protocol [20].iii.The d2 Test of Attention will be performed on paper and its results will be calculated according to a standardized manual [21, 22].iv.Visual attention test will be performed using virtual reality glasses according to standardized procedure and assessment [23].v.Paper-based Karolinska Sleepiness Scale (Version A) questionnaires will be provided and assessed according to the validated procedure [24].vi.Validated Stanford Sleepiness Scale questionnaires will be completed on laptops and follow a simple seven-scale choice [25].vii.The EEG data, complemented by the polysomnographic (PSG) recording of electrooculogram (EOG), electromyogram (EMG), and electrocardiogram (ECG), will be collected with SIENNA® Ultimate amplifier systems (EMS Biomedical, Korneuburg, Austria) and analyzed with dedicated software for the visual scoring of sleep variables (e.g., alphatrace NeuroSpeed-PSG, alpha trace medical systems, Vienna, Austria). During the driving simulation, EEG data will be recorded using a mobile Philips ALICE 6 device (Philips AG Sleep and Respiratory Care, Zofingen, Switzerland). According to standard international criteria, sleep stages will be scored for each night in the laboratory, and validated sleep variables reflecting sleep quality (e.g., total sleep time, sleep latency, length of non-rapid-eye-movement (NREM) and rapid-eye-movement (REM) sleep stages, waking time after sleep onset, sleep efficiency) will be derived and compared between the conditions [26]. Labmade software will be used for the quantitative analysis of the EEG.viii.Blinded and pre-instructed assessors will collect the behavioral abnormalities of participants after the driving simulation test on paper. They will rate orientation, coordination, speech, mood, appearance, reaction, and eye reactions to light according to standardized options.ix.Unstimulated finger sweat will be collected using self-punched sampling units made of filter paper. Samples will be handled and analyzed analogously to oral fluid samples.x.Exhaled breath samples will be collected in specialized devices from SensAbues AB (Stockholm, Sweden) and BreathExplor® (Munkplast AB, Uppsala, Sweden). Dried blood spots will be collected on volumetric cards (Capitainer, Solna, Sweden). All samples will be handled and analyzed analogously to oral fluid samples.

### Plans to promote participant retention and complete follow-up {18b}

Appointments for study interventions will be scheduled with the participants directly after successful completion of screening, and a personal reminder will be sent in advance. Financial compensation will be paid per complete study arm and increases to promote retention. Participants will also be offered presentation of study results after completion, if interested.

For participants deviating from intervention protocols, non-adherence will be recorded in the CRF. If deviations concern sleep regime, all outcome data will be excluded from further analysis.

### Data management {19}

SOP instruct the entire study personnel on how to make data entries to eliminate differences. Protocol procedure data will be collected in a pseudonymized paper CRF where all entries have to be signed and dated by study personnel. Raw data of performance tests and biological specimen analyses will be stored digitally on local computers with access rights restricted to study personnel only. Two independent study employees will digitalize the results of paper-based performance tests and questionnaires after every session. Daily backups of local IT infrastructure secure digital data. Additional backups of digital raw data on password-secured and encrypted external hard drives are automatically run.

All original digital data and paper records, such as CRF, consent forms, and relevant correspondence, will be archived at the sponsor’s institute for a minimum of 10 years after trial completion, according to local regulations.

### Confidentiality {27}

Participants will be allocated an individual ID number after providing written informed consent. This allocation will be kept secure in a password-protected and access-restricted identification log file. Copies of written informed consent forms will be stored separately from study records in restricted area. All other documents, files, labels, and specimens will only contain participants’ ID numbers and are therefore pseudonymized. During the trial period in the sleep laboratory, participants will wear their individual ID number visible on clothing.

Suspension of confidentiality can only be initiated with written permission of the participant or for the purpose of monitoring and audits by entitled authorities.

### Plans for collection, laboratory evaluation, and storage of biological specimens for genetic or molecular analysis in this trial/future use {33}

The coded biological specimens will be stored refrigerated for a maximum of 10 years after trial completion at the Zurich Institute of Forensic Medicine, University of Zurich, Switzerland, and will be destroyed thereafter. Decryption is not foreseen, except by personal request and written permission of respective participant.

## Statistical methods

### Statistical methods for primary and secondary outcomes {20a}

Based on our study design, statistical analysis will be performed to detect both intra- and inter-individual (i.e., individual and group) differences. All the analyses will be carried out in reference to hours of wakefulness (i.e., clock time), and also in reference to the internal body time (IBT) of the participants which is determined by the dim light melatonin onset (DLMO) from oral fluid samples.

The primary outcome of the trial is the changes detected in the metabolome. Concentration values of metabolic features will be used to generate feature time series. As a first characterization, the rhythmicity of features will be tested by cosinor analysis. Other regression models such as linear, exponential, or logarithmic functions will be applied for fitting time series data in order to simplify complex patterns. To extract relevant features from the time series, different statistical approaches will be carried out. Firstly, we will investigate how group-level differences vary when applying generalized linear mixed models and — if group-level differences exist — conduct multiple comparison tests. After applying the corrections for multiple testing (Benjamini–Hochberg procedure, i.e., false discovery rate), adjusted p-values will be considered significant when below 0.05. Significant features will then be shortlisted. Secondly, each time series will be checked for the occurrence of regular patterns (e.g., linear increase/decrease, exponential, etc.) in relation to hours of wakefulness. Again, each feature candidate will be added to the shortlist. Lastly, a classification task will be carried out to isolate those features leading to a separation between the study arms. The result of the primary outcome will be a list of candidate biomarkers.

For secondary outcomes, differences between study groups will be reported. For variables that are continuous (i.e., outcome of PVT, d2-task, driving simulator parameters, EEG data) the mean and the median will be computed accordingly. For variables that are either binary or ordinal (i.e., results of the behavioral impairment test, visual attention test, sleepiness scales, expert decision on driving ability), the relative frequencies, proportions, and standard errors for each group will be reported.

Regarding the metabolic correlation between blood and non-invasive specimens as a secondary outcome, a regression analysis will be performed between metabolite concentration values in blood and in other sampled matrices.

As a last step, causality between all outcomes will be tested by cross-correlation analyses.

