Secondary outcome measures will include:i.Driving performance: Investigators will gather driving simulation results via Standardized Application for Fitness to Drive Evaluations (S.A.F.E.) [17–19], and analyze their changes after sleep deficit in comparison to the control condition. Driving simulation test is scheduled once per study arm, in the morning after the experimental night (10 am).ii.Psychomotor vigilance test (PVT) [20]: The PVT is a gold standard reaction time test to assess vigilance and sustained attention. It will be performed after arrival at the study site (6 pm, baseline), repeatedly during scheduled wakefulness (8 am, 12 pm, 4 pm, 7 pm, 11 pm), and in the morning after recovery night (8 am).iii.d2 Test of Attention [21, 22]: The d2 Test of Attention is a paper and pencil test to assess selective and sustained attention and visual scanning speed. It is scheduled after arrival at the study site (6 pm, baseline), repeatedly during scheduled wakefulness (8 am, 12 pm, 4 pm, 7 pm, 11 pm), and in the morning after recovery night (8 am).iv.Visual attention test [23]: The visual attention test is a virtual reality glasses test to assess visual skills in a complex visual environment. It will be conducted after arrival at the study site (8 pm, baseline), repeatedly during scheduled wakefulness (10 am, 2 pm, 6 pm, 8 pm), and in the morning after recovery night (8 am).v.Subjective situational sleepiness: Participants will complete the Karolinska Sleepiness Scale (KSS) [24] questionnaire after arrival at the study site (6 pm, baseline), repeatedly during scheduled wakefulness (8 am, 12 pm, 4 pm, 7 pm, 11 pm), and in the morning after recovery night (8 am).vi.Subjective sleepiness: Participants will complete the Stanford Sleepiness Scale (SSS) [25] questionnaire after arrival at the study site (6 pm, baseline), repeatedly during scheduled wakefulness (8 am, 12 pm, 4 pm, 7 pm, 11 pm), and in the morning after recovery night (8 am).vii.Electroencephalographic (EEG) changes: Investigators will analyze changes in sleep and wake EEG patterns of participants by calculating sleep scores according to the American Academy of Sleep Medicine (AASM) scoring manual [26]. EEG recordings will be performed during scheduled sleep, driving simulation test (10 am), and at two time points during scheduled wakefulness (12 pm, 7 pm).viii.Behavioral markers of drowsy driving: Investigators will examine participants immediately after the driving simulation test for behavioral abnormalities concerning orientation, coordination, speech, mood, appearance, reaction, and pupillary light reflex.ix.Changes in metabolite concentrations in exhaled breath: Investigators will collect exhaled breath samples from participants for quantification of all detectable metabolites after arrival at the study site (8 pm, baseline), repeatedly during scheduled wakefulness (10 am, 2 pm, 6 pm, 8 pm, 11 pm), and in the morning after recovery night (8 am). They will analyze which metabolite concentration values undergo significant changes during sleep deficit conditions sessions in comparison to the control condition and also show the effects of recovery sleep. These will serve as secondary candidate biomarkers.x.Changes in metabolite concentrations in finger sweat: Investigators will collect finger sweat samples from participants for quantification of all detectable metabolites after arrival at the study site (8 pm, baseline), repeatedly during scheduled wakefulness (10 am, 2 pm, 6 pm, 8 pm, 11 pm), and in the morning after recovery night (8 am). They will analyze which metabolite concentration values undergo significant changes during sleep deficit conditions sessions in comparison to the control condition and also show the effects of recovery sleep. These will serve as secondary candidate biomarkers.xi.Correlation of metabolic changes between blood and non-invasive specimens: Investigators will compare metabolite concentrations in non-invasive matrices (oral fluid, finger sweat, exhaled breath, and dried blood spots) and compare those with a blood sample. The collection of specimens for this outcome is scheduled immediately after the driving simulation test in each study arm.

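### The sleepiness scales (KSS, SSS) are called ordinal but get the same per-arm proportions as yes/no results; no within-participant contrast on the ordered scale is named (minor, secondary outcomes)

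*Protocol article*

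**What the plan says.** Section {20a} sorts the secondary outcomes by type of variable. Continuous outcomes are summarised by location: "the mean and the median will be computed accordingly". A second rule covers the rest. It begins "For variables that are either binary or ordinal (i.e., results of the behavioral impairment test, visual attention test, sleepiness scales", also takes in the expert decision on driving ability, and ends: "the relative frequencies, proportions, and standard errors for each group will be reported".

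The plan therefore labels the sleepiness scales ordinal itself. Section {18a} gives the SSS seven levels: the "questionnaires will be completed on laptops and follow a simple seven-scale choice". It does not state the number of KSS levels. Section {12} schedules both scales at seven times per arm: baseline, five times during wakefulness, and the morning after recovery sleep.

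Two general statements also apply. The paragraph on secondary outcomes opens with "For secondary outcomes, differences between study groups will be reported". Section {20a} as a whole opens by saying that "statistical analysis will be performed to detect both intra- and inter-individual (i.e., individual and group) differences". The section ends with cross-correlation among all outcomes.

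**The concern.** For a yes/no result, a proportion with its standard error is the natural summary. For a seven-level ordered score it describes one level or one cut at a time. It does not say by how much the same man's score rose from his control session to his deprivation or restriction session, which is what a crossover is built to estimate.

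KSS and SSS are the trial's only self-reports of sleepiness, and they are taken at all seven oral-fluid sampling times. They show directly whether each deficit arm, the restriction arm included, produced the felt state that the candidate biomarkers are meant to indicate. If the report consists of proportions per arm, a modest upward shift is spread over several cells. At middle levels it partly cancels, because some men enter from below while others leave upward.

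**Working it through.** **1. The plan's own figure.** Section {14} gives 17 participants for 80% power at α = 5%, from a preliminary metabolite analysis, and a target of 24. It states no effect size or standard deviation, so 17 cannot be reproduced. It can only be solved backwards. With a paired t-test and the noncentral t distribution, n = 17 and 80% power correspond to a mean difference of 0.72 standard deviations of the difference (two-sided) or 0.63 (one-sided). At n = 24 that effect has about 92% or 91% power. This figure concerns metabolites. The article gives no effect size, power or sample size for KSS or SSS, so every shift below is an assumption.

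**2. Precision of one level.** With 24 men and seven levels, the average is 24/7 = 3.4 men per level. A level held by 1/7 of the men (14.3%) has standard error √[(1/7)(6/7)/24] = 0.071, or 7.1 percentage points, half the proportion itself.

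**3. Effect of the scale alone, all tests paired.** Simulation with 3,000 replicates per setting: latent normal sleepiness with unit variance and within-man correlation 0.5, cut into seven levels at six equally spaced points from −1.8 to 2.2. One level is then (2.2 + 1.8)/5 = 0.8 standard deviations wide, so the three shifts below equal 0.5, 0.75 and 1 level. One time point, n = 24, two-sided 5%.

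| Latent shift | Signed-rank, full scale | Best of six cuts | Best single level |
|---|---|---|---|
| 0.4 | 43% | 31% | 13% |
| 0.6 | 76% | 56% | 20% |
| 0.8 | 94% | 79% | 30% |

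An independent rerun with 2,000 replicates gave 44/29/12, 76/55/19 and 94/78/31. Over n = 17 or 24, correlations 0.3 to 0.7 and shifts 0.4 to 0.8, the full scale gains about 3 to 32 points over the best cut. The comparison favours the cut, because the best one was picked after the fact and its Wald test rejected in 5 to 8% of null samples, against 4 to 5% for the signed-rank test.

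**4. Larger shifts, in scale points.** A second simulation (1,000 replicates, n = 24, correlations 0.3 and 0.5) used rounded scores. Assumptions: KSS with nine levels, control mean 4, standard deviation 1.5, cut at 7 or more; SSS with seven levels, mean 2.5, standard deviation 1.2, cut at 5 or more.

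| Scale, shift | Signed-rank (paired, ordered) | Chi-square on levels (unpaired, unordered) | Exact McNemar at the cut |
|---|---|---|---|
| KSS 1.0 | 73–84% | 14–16% | 6% |
| KSS 1.5 | 97–100% | 46–48% | 32–33% |
| KSS 2.0 | 100% | 82–84% | 74–79% |
| KSS 3.0 | 100% | 100% | 99–100% |
| SSS 1.0 | 88–97% | 41–43% | 15–17% |
| SSS 1.5 | 100% | 85–89% | 63–72% |
| SSS 2.0 | 100% | 99% | 96–98% |

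The gaps here are wider than in step 3 for reasons other than ordering. The chi-square also ignores the pairing, the cut is fixed and may be badly placed, and both comparators are conservative (null error 2 to 4% and about 0%). Step 3 is the cleaner measure of what the scale costs. Step 4 shows that the loss fades as the shift grows.

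**The case against.** The strongest reply is that the sentence describes reporting, not testing. It names no test, no cut-point and no level-by-level comparison for the scales, and the continuous outcomes are likewise given summaries without a test. A frequency table over ordered levels preserves the whole distribution, and median, quartiles and cumulative proportions can be read from it. The trial is exploratory. Candidate biomarkers are chosen by contrasts between sleep conditions, not by KSS or SSS. Vigilance, attention, EEG, driving and behavioural measures also bear on sleepiness, and a fuller protocol or analysis plan may name a model.

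Most of this stands. A reader might infer that the plan throws away the ordering and much of the power to show that the men became sleepier. The documents do not support that: the table keeps the order, and no planned test exists whose power could fall. Nor does the metabolite effect size of 0.72 say anything about felt sleepiness.

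One part remains. The article does not leave the summary of these scales open. It assigns them one, and it is the one suited to binary results. The general aim of studying intra-individual differences and the closing cross-correlation do not supply an ordered contrast between arms, and tables per arm do not show how far each man moved.

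**Conclusion.** The point holds as a minor improvement to secondary outcomes. The summary named for KSS and SSS does not use their order to estimate the shift between conditions. The primary outcome is unaffected, and no stated power is lost.

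The size is conditional on arms being compared level by level or at a cut. With pairing held constant, n = 24 and correlation 0.5, the assumed shifts of half to one level cost 12 to 20 points of power against the best cut (43−31, 76−56, 94−79), and more against single levels. At n = 24 and 2 points, an unordered comparison costs about 1 point on SSS and 16 to 18 on KSS, part of it due to lost pairing; at 3 points nothing is lost. At n = 17 the 2-point KSS loss is larger (99–100% against 53–54%). All of this rests on assumed shifts, correlations, cut-points and control distributions, and on nine KSS levels; the documents give none of these.

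**What to change.** In {20a}, restrict proportions with standard errors as the main summary to truly binary results, such as the expert decision on driving ability. For KSS, SSS and any other ordered score in that list:

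- keep the frequency tables and add median and quartiles;
- report each deficit arm's within-participant shift from control with a 95% confidence interval, either from a cumulative-logit (or linear) mixed model with condition, time point and a participant random effect, or from a signed-rank contrast;
- state at which time point or points the shift is taken.

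The cost is a change of wording and a little more analysis, with no new data, visits or participants. The cumulative-logit model assumes one odds ratio across all cut-points of the scale. The retained frequency tables allow that to be checked.
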